### Recruitment and consent

Eligible patients will be identified during hospitalization or outpatient visits. The investigators will explain the study objectives, procedures, and rights. Written informed consent will be obtained from all participants or guardians. Procedures and interventions.

### Study flow

Baseline assessment (T0):

Socio-demographic and clinical data collectionAudio-recorded clinical interviewClinical rating scales: PANSS (Positive and Negative Syndrome Scale), BPRS (Brief Psychiatric Rating Scale), CDSS (Calgary Depression Scale for Schizophrenia), MADRS (Montgomery–Åsberg Depression Rating Scale), Altman, YMRS (Young Mania Rating Scale), GAF (Global Assessment of Functioning), SF-36 (36-Item Short Form Survey), CGI-S (Clinical Global Impression Scale)Blood samples collected during routine care: inflammatory biomarkers (IL-1, sIL-2R, IL-4, IL-6, IL-8, TNF), C-reactive protein, vitamin DBiobanking: plasma (2 EDTA tubes, 6 mL each) and serum samples (2 SST tubes, 5 mL each) stored at the Biological Resource Center (CHU Brest). Blood samples are processed following the standard operating procedures of the certified biobank of the CHU de Brest, in accordance with the national NF S96–900 and ISO 20387 guidelines. In routine practice, EDTA tubes (for plasma) and SST tubes (for serum) are centrifuged shortly after collection, aliquoted under sterile conditions, and stored at –80 °C until batch analysis.

Follow-up assessments:

12 months (T1): Telephone or in-person diagnostic interview and treatment update24 months (T2): Diagnostic interview, treatment update, and clinical rating scales

### Clinical rating scales

#### PANSS (Positive and Negative Syndrome Scale)

The Positive and Negative Symptom Scale is a 30-item scale, rated from 1 (absent) to 7 (extreme), which assesses psychopathological symptoms observed in patients with psychotic conditions, particularly schizophrenia. It allows scores to be calculated for three dimensions: positive symptoms (seven items), negative symptoms (seven items), and general psychopathology (16 items). Positive symptoms refer to an excess or distortion of normal functions (e.g., hallucinations), and negative symptoms represent a decrease or loss of normal functions. Its use is particularly indicated for determining a psychopathological profile, researching prognostic factors for progression, and evaluating the effectiveness of various therapeutic strategies (45).

#### BPRS (Brief Psychiatric Rating Scale)

The Brief Psychiatric Rating Scale is a rapid and highly effective assessment procedure to evaluate symptom changes in psychiatric patients. It includes a precise and comprehensive description of major characteristic symptoms. The factor analyses of the 18 items of the BPRS usually provide four or five underlying factors. The Diagnostic and Psychopathology Unit at the Clinical Research Centre in Los Angeles has developed an expanded version of the BPRS with 24 questions (46).

#### CDSS (Calgary Depression Scale for Schizophrenia)

The Calgary Depression Scale for Schizophrenia is designed to assess depression in this patient population. It consists of nine questions rated from 1 (absent) to 3 (severe), for which the effects of negative symptoms, psychotic symptoms, or treatment should be reduced, which is not the case with other scales (47).

#### MADRS (Montgomery–Åsberg Depression Rating Scale)

The Montgomery–Åsberg Depression Rating Scale is a scale used to assess the severity of depression in patients with mood disorders. It is also frequently used to measure changes brought about by depression treatment. It assesses the severity of symptoms in a wide range of areas such as mood, sleep, and appetite, physical and mental fatigue, and suicidal thoughts (48).

The scale consists of 10 items rated from 0 to 6:

- 0 to 6 points: The patient is considered healthy.- 7 to 19 points: The patient is considered to have mild depression.- 20 to 34 points: The patient is considered to have moderate depression.- >34 points: The patient is considered to have severe depression.

#### Altman

The Altman Self-Assessment Scale is a short five-point self-assessment questionnaire (scored from 0 to 4) that can be useful for assessing the presence and severity of manic or hypomanic symptoms. As this scale is compatible with diagnostic criteria, it can be used effectively as a screening and diagnostic tool despite its brevity. Each of the five items is scored from 0 to 4 (49, 50).

#### YMRS (Young Mania Rating Scale)

The Young Mania Rating Scale comprises 11 items used to assess the severity of mania. The manic symptoms evaluated are euphoria, increased activity/motor energy, sexual interest, sleep, irritability, speech (rhythm and quantity), language disorders, thought content, behavioral alteration/aggressiveness, appearance, and lucidity.

The items 1, 2, 3, 4, 7, 10, and 11 are rated from 0 (no symptoms) to 4 (extreme symptoms). The items 5, 6, 8, and 9 are rated from 0 (no symptoms) to 8 (extreme symptoms). A precise description is given for each point on the scale. An overall score is calculated by adding up the scores for each item: [0–20] non-manic patient, [20–26] mild intensity, [26–38] moderate intensity, and [38 and above] severe intensity (51).

#### GAF (Global Assessment of Functioning)

The Global Assessment of Functioning scale is used to assess the severity of a mental illness. It determines the extent to which a person’s symptoms affect their daily life on a scale of 0 to 100. Its results help caregivers determine the level of care a person may need as well as the effectiveness of certain treatments (52).

#### SF-36 (36-item short form survey)

The SF-36 questionnaire is a standardized test to measure the quality of life. It contains 11 items rated from 0 to 6 (53).

#### CGI-S (Clinical Global Impression Scale) and CGI-I (CGI-Improvement)

The CGI-S and GCI-I scales are widely used in psychopharmacology. They enable clinicians to assess improvements in a patient’s condition over time after prescribing treatment or discontinuing it (54).

### Outcomes

#### Primary outcome

• Affective *vs*. non-affective evolution of psychosis at 2 years based on prosodic markers at baseline:

Fundamental frequency (F0) variabilitySpeech latency (mean response time and coefficient of variation)

#### Secondary outcomes

• Affective *vs*. non-affective evolution of psychosis at 2 years based on:

Syntactic and semantic markers (8)Inflammatory biomarkers (39)Clinical scales

### Data collection and management

Data will be collected in electronic case report forms (eCRF). Interviews will be transcribed verbatim and analyzed using natural language processing (NLP) methods developed with IMT Atlantique (55). Biological samples will be processed and stored according to standardized protocols. Data confidentiality will be ensured through anonymization and compliance with the GDPR (General Data Protection Regulation).

### Statistical analysis

Statistical analyses will be performed with SAS 9.4 and R (version 4.0.4). All patients included will be analyzed according to the intention-to-treat principle.

Primary analysis: Logistic regression models will evaluate the predictive value of prosodic markers (F0 variability, response latency). Model performance will be assessed using calibration and discrimination indices.Secondary analyses: Univariate logistic regressions will be conducted for syntactic/semantic markers, inflammatory biomarkers, and clinical scales. Variables with *p <*0.15 will be included in multivariate models. Stepwise backward elimination will retain predictors with *p <*0.05.

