## Methods and analysis

### Study design

The PEPAMARKER is a multicenter, prospective cohort study conducted in five psychiatric centers in France. The study is categorized as minimal risk and little constraint, in compliance with the French and international Good Clinical Practice guidelines. Based on Riley et al. (41), 217 participants are required to achieve sufficient statistical power to develop a multivariable prediction model with three candidate predictors, assuming 17% affective psychoses (2) and expected *R*² of 0.3 (42, 43). Participants with first-episode psychosis (FEP) will be included and followed for 24 months, with assessments at baseline, 12 months, and 24 months.

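### The secondary analyses pick predictors with two p-value filters from at least 16 candidates on about 37 events: selection will be unstable, coefficients too extreme and apparent performance inflated

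*Protocol article*

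**What the plan says.** Study design in the protocol article states that "217 participants are required to achieve sufficient statistical power to develop a multivariable prediction model with three candidate predictors", "assuming 17% affective psychoses" and "expected *R*² of 0.3". It does not say which R² is meant.

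Statistical analysis then fixes a rule for the secondary predictors, which are syntactic/semantic markers, inflammatory biomarkers and clinical scales. After univariate logistic regressions, variables with p < 0.15 "will be included in multivariate models. Stepwise backward elimination will retain predictors with" p < 0.05. That section mentions no shrinkage, penalisation or optimism correction. Calibration and discrimination are named only under the primary analysis.

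Study flow lists what is measured at baseline: "inflammatory biomarkers (IL-1, sIL-2R, IL-4, IL-6, IL-8, TNF), C-reactive protein", vitamin D, and nine scales (PANSS, BPRS, CDSS, MADRS, Altman, YMRS, GAF, SF-36, CGI-S). The number of syntactic and semantic features is not given. The Abstract announces an assessment of internal validity without a method. The Discussion says that 217 patients allow a robust multivariable model.

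**The concern.** The sample size was justified for three candidates, but the secondary rule searches at least 16. Choosing predictors twice by p-value on the same few events has three known effects. Noise variables survive by chance, the coefficients of the survivors are too large because only large estimates pass, and performance in the development data looks better than it will in new patients. A univariate screen also discards variables that matter only jointly. The sizing method that the article cites counts every candidate examined, not only those that survive.

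Every claim about inflammatory, linguistic (other than prosodic) and clinical-scale predictors rests on this rule. The Dissemination plan promises clinicians validated tools that include laboratory tests, and nothing labels the secondary models as exploratory.

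**Working it through.** **Inputs.** From Study design: N = 217, 3 candidates, prevalence 0.17, R² = 0.3. From Study flow: 9 scales + 6 cytokine markers + CRP = 16, or 17 with vitamin D; by block, 8 blood markers and 9 scales. From Statistical analysis: thresholds 0.15 and 0.05. Assumed, because not stated: R² as either Cox–Snell or Nagelkerke, a 0.05 margin for overall risk, and the effect sizes and correlations in the simulations.

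**Events.** 217 × 0.17 = 36.9. Per candidate: 36.9/3 = 12.3; 36.9/8 = 4.6; 36.9/9 = 4.1; 36.9/16 = 2.3; 36.9/17 = 2.2. Assumed losses of 10–30% would leave 33 to 26 events.

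**Reproducing 217.** The precision criterion gives n = (1.96/0.05)² × 0.17 × 0.83 = 216.8, so 217. This criterion does not depend on the number of predictors. The two criteria that do are:
- shrinkage: n = P / ((S − 1) ln(1 − R²/S)) with S = 0.9;
- optimism: the same formula with S = R²/(R² + 0.05 × max R²), where max R² = 0.598.

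Read as Nagelkerke, R² = 0.3 corresponds to a Cox–Snell value of 0.3 × 0.598 = 0.179. Example, 17 candidates, Cox–Snell, shrinkage: 17/(0.1 × 0.4055) = 419.3, so 420.

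| Candidates | Cox–Snell: shrinkage / optimism | Nagelkerke: shrinkage / optimism | Expected shrinkage at 217 (C–S / Nag.) |
|---|---|---|---|
| 3 | 74 / 83 | 135 / 90 | 0.96 / 0.94 |
| 8 | 198 / 221 | 360 / 239 | 0.91 / 0.85 |
| 9 | 222 / 248 | 405 / 269 | 0.90 / 0.83 |
| 16 | 395 / 441 | 720 / 477 | 0.83 / 0.74 |
| 17 | 420 / 469 | 765 / 507 | 0.83 / 0.72 |

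So 217 covers three candidates comfortably. It falls short of 441–720 (16) or 469–765 (17) for a pooled model, and of 221–248 (Cox–Snell) or 360–405 (Nagelkerke) for a block of 8 or 9.

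**Pure noise, by arithmetic.** With k independent null candidates, the chance that at least one reaches p < 0.05 is about 1 − 0.95^k: 34% for 8, 37% for 9, 58% for 17.

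**Simulation of the stated rule.** N = 217, prevalence 0.17, normal predictors with pairwise correlation 0 / 0.3, 400 replicates per cell, new-data performance on 10,000 subjects, averaged over replicates in which a model was retained. Modest and stronger signal mean three equal true predictors, with the standard deviation of the linear predictor 0.8 and 1.25.

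| Candidates, signal | Model retained | Apparent AUC | New-data AUC | Calibration slope | Noise variable kept |
|---|---|---|---|---|---|
| 17, none | 62% / 59% | 0.641 / 0.642 | 0.500 / 0.500 | 0 / 0 | all |
| 17, modest | 99% / 100% | 0.732 / 0.717 | 0.645 / 0.657 | 0.59 / 0.70 | 56% / 47% |
| 17, stronger | 100% / 100% | 0.805 / 0.798 | 0.768 / 0.747 | 0.83 / 0.77 | 48% / 40% |
| 8, none | 35% / 32% | 0.628 / 0.631 | 0.501 / 0.501 | 0.01 / 0.00 | all |
| 8, modest | 98% / 99% | 0.713 / 0.718 | 0.655 / 0.679 | 0.71 / 0.82 | 26% / 21% |
| 8, stronger | 100% / 100% | 0.802 / 0.793 | 0.765 / 0.756 | 0.83 / 0.84 | 22% / 18% |

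Repetitions, with log odds ratios of 0.5, 0.4 and 0.3 per SD as the modest signal, gave a noise-only model from 17 candidates in 54–60% of studies. For three true among 17, slopes ran from 0.53 (the pessimistic end) to 0.74. For single blocks of 8 or 9, a noise-only model appeared in 28–38% of studies, and slopes with modest signal were about 0.67–0.83. With 30 candidates (assuming 13 linguistic features), a noise-only model appeared in 77–78%, and slopes with true signal were 0.51–0.74.

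**The case against.** Four points on the other side carry weight.

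- *Internal validation is announced.* A reader might infer that the reported performance of the secondary models will be inflated. The article does not support that: the Abstract plans an assessment of internal validity, and its method and scope may properly sit in the full protocol or SAP. If it repeats the screening and elimination in every resample, reported performance can be corrected. Inflation is certain only for apparent performance. Even a full bootstrap, however, leaves the selection unstable and the coefficients too extreme.
- *The models may be separate.* It is tempting to put all 17 candidates into one model at 2.2 events each and cite 469–765 as the required size. The article speaks of models in the plural and lists three blocks under Secondary outcomes, so a pooled model is only one reading. Per block the shortfall is small under Cox–Snell and clear under Nagelkerke. Across the two countable blocks, the chance of at least one spurious predictor if all 17 were independent noise is still about 58%.
- *The magnitudes depend on unstated inputs.* Effect sizes and correlations are not in the article. With stronger signal the slope for 17 candidates rises to 0.77–0.83. Pure noise is an extreme case, since mania and depression scales plausibly relate to an affective outcome. Overlapping scales may also correlate above 0.3.
- *Only secondary analyses are affected.* A reader might conclude that the study is undersized for its main purpose. It is not shown to be: the filters do not touch the primary prosodic model, and a study sized for its primary model is not wrong because the secondary models would need more patients.

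**Conclusion.** The concern holds for the secondary models and should be fixed, though it does not threaten the primary analysis. The rule is stated outright, so an SAP that follows it would carry it out rather than cure it. On about 37 events, it will give unstable selection, over-extreme coefficients and inflated apparent performance under either reading of how the models are built. The size is illustrative. For 17 candidates taken together, a noise-only pool yields a model in about 54–62% of studies with apparent AUC about 0.64 against 0.50, and modest signal gives slopes of about 0.55–0.75. For a block of 8 or 9, the figures are about 28–38% and about 0.67–0.83.

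The candidate count is a lower bound. Linguistic features, subscales, loss to follow-up and the confounder adjustment promised under Risk assessment would all worsen the ratio.

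**What to change.** Replace the p < 0.15 and p < 0.05 filters with one penalised logistic model per block of candidates listed in advance: ridge, or elastic net if variable selection is wanted. In the planned internal validation, bootstrap the whole procedure, including penalty tuning and any selection, and report optimism-corrected AUC and calibration slope. Keep the univariate odds ratios as description, and label the secondary models exploratory. In the Discussion, limit the claim of a robust multivariable model to the three-predictor primary model.

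In one simulated comparison (three true predictors among 17), ridge and the stepwise rule had the same new-data AUC, 0.62, but slopes of 0.98 and 0.53. With eight weak predictors, ridge had AUC 0.62 and slope 1.17, against 0.58 and 0.39. Ridge is therefore not perfectly calibrated either, but it was closer to 1 in both settings.

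The cost is a change of wording and a few lines of R, which the article already names; design, sample and data collection stay as they are. Penalised coefficients carry no conventional p-values, ridge makes no hard selection, and the reported performance will look slightly less favourable. The change should be made before outcomes are analysed, so that it cannot appear data-driven.

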### Risk assessment

A methodological risk analysis was conducted to identify potential sources of bias in this multicenter prospective study. Selection bias may occur due to the inclusion and exclusion criteria, which could limit the representativeness of the broader first-episode psychosis population; this risk is mitigated through consecutive recruitment across centers using homogeneous eligibility procedures. Measurement bias is possible in both clinical assessments and speech-related measures, given differences in interviewing conditions, rather interpretation, or audio quality. To reduce this variability, all assessments rely on standardized scales administered by trained clinicians, and recorded interviews follow a uniform procedure, with biological samples processed according to established protocols in the certified biobank. Attrition bias is another anticipated challenge given the 24-month follow-up; the protocol allows a 12-month telephone visit and collects any available clinical information to limit missing diagnostic outcomes. Differences between centers may also introduce heterogeneity in patient profiles or clinical practices; this is addressed through harmonized procedures, central transcription of interviews, and regular monitoring ensuring adherence to the protocol. Finally, confounding factors such as psychotropic treatments, baseline symptom severity, or socio-demographic characteristics are documented systematically and will be accounted for in multivariable statistical modeling. The combination of these measures is intended to mitigate the primary methodological risks while maintaining the ecological validity of the study conducted in routine clinical settings.

## Discussion

The PEPAMARKER study addresses one of the central challenges in early psychosis care: the difficulty of distinguishing affective trajectories. Early differentiation is crucial, as treatment strategies and prognoses differ substantially between these subgroups.

A major strength of this study is its multimodal approach, combining clinical interviews, linguistic analyses, and inflammatory biomarkers. While linguistic markers have already shown promise in distinguishing between schizophrenia and bipolar disorder (5, 6), their predictive value in real-world FEP cohorts remains to be established. Similarly, inflammatory markers have been reported to differentiate affective psychoses (39).

Another strength lies in the ecological design: assessments are based on routine clinical interviews and simple blood tests, ensuring feasibility and acceptability in everyday psychiatric practice. The sample size (217 patients across the five centers) makes it possible to develop a robust multivariable predictive model (41).

Several limitations must, however, be acknowledged. First, the study only includes French-speaking participants. As linguistic markers are language-dependent, the predictive characteristics identified in French may not be generalizable to other languages. Second, the naturalistic type/kind/character of the cohort implies heterogeneity of treatments during follow-up, which may induce variability. The study also carries a risk of follow-up losses, as visits are spaced out over 2 years in a population often at the beginning of their care pathway where building a therapeutic alliance is a major challenge. Furthermore, the question of how inflammatory markers evolve over time may arise, as these are recently identified indicators that are still being explored scientifically. Another limitation relates to the symptomatology of first-episode psychosis and the fact that the patients included are not yet receiving treatment—that is, some patients may call into question their ability to consent or to be present for the initial assessments. This doubt or uncertainty likely exposes them to a selection bias, as the most severe forms are often treated immediately. From an ethical standpoint, it is worth mentioning the risk of de-subjectification of the patient, with the fear of a loss of clinical meaning in favor of computational approaches (56). Finally, other potential predictors such as brain imaging (57) are not included.

Despite these limitations, the present study is relevant to evaluate a wide range of clinical and paraclinical markers in routine care settings. These elements are easy to collect and minimally intrusive for patients. The proposed management is in line with usual practice, including the recording of a clinical interview. The only examination specific to the study is the search for inflammatory markers, which can, however, be easily integrated into the standard biological assessment carried out during first-episode psychosis.

The PEPAMARKER is expected to advance our understanding of early predictors of psychosis trajectory and generate accessible clinical tools for early differentiation. This project stands out due to the joint integration of three types of markers that are rarely combined: linguistic, clinical, and inflammatory. Automated language analysis, applied to first-episode psychosis, is an emerging and promising field (58). Few studies have sought to distinguish early affective and non-affective psychoses using biomarkers from a simple recorded clinical interview. The proposed multimodal approach provides an innovative way to explore the pathophysiology of first-episode psychosis and paves the way for objective standardized predictive tools that can be used soon after the patient is admitted.

The tools evaluated in this study, a recorded clinical interview and standard biological assessment, can be easily integrated into routine practice and do not require specialized technological resources other than a data processing pipeline currently undergoing automation. Their accessibility facilitates their deployment in various clinical contexts, including in facilities with limited resources.

In organizational terms, the potential benefits for the healthcare system are significant. Early differentiation between affective and non-affective psychoses is a major challenge, as it determines the speed and relevance of therapeutic strategies (40, 59). Reducing diagnostic uncertainty would limit relapses, repeated hospitalizations, and interruptions in treatment, with a direct impact on the workload of psychiatric services (60, 61).

